**Theoretical Adverse Effects With No Documented Events**

*a) Effects on blood glucose:* arginine stimulates both insulin and glucagon release53. Because levels of glucagon increase to levels higher than that of insulin, the net effect in humans is reported to be a slight hyperglycemia32,53. Importantly, despite over 40 years’ of use of intravenous arginine in humans, there are **no** clinical case reports of hypoglycemia ever occurring after arginine infusion.

Hypoglycemia can occur in severe (but not, by definition, in uncomplicated malaria)2, therefore blood glucose will be rigorously monitored in both studies as outlined in table 2: We will use iSTAT cartridges (which use a few microlitres of blood) at the bedside to instantly measure glucose (as well as other electrolytes) prior to infusion, at the end of the 30 min infusion, and 15, 30, 60 and 210 minutes after the end of the infusion. Because levels of glucagon (which increases glucose) are higher after arginine infusion than insulin (which lowers glucose), if anything arginine may help prevent hypoglycemia in malaria. We will be measuring glucose in stage 2 and 3 in uncomplicated malaria, so can report back to the ethics committee the effect on blood glucose in malaria before we give arginine to anyone with severe malaria in future studies. If anything the glucagon effect *increasing* blood sugar is likely be protective.

Response: If blood glucose falls below 4 mmol/L, the arginine infusion will be stopped and 50% dextrose will be administered as per standard RSMM/MoH practice in severe malaria, with blood glucose continuing to be monitored 15 minutely to 60 mins then 30 minutely until 480 mins.

*b) Effect on pH:* Arginine hydrochloride contains H+ ions (4.75 mEq/g). While there is a *theoretical* potential for acidosis there have been no reports of this. Hertz *et al* (1972) 56 carefully documented the effect of IV arginine on arterial pH. They found **no change** in the pH despite infusion of 30g (much higher than we will use in this study) and despite the fact they infused arginine into patients with renal failure – who are at risk for acidosis56. Clinically significant change in pH has not been found except in patients with hypochloremic alkalosis (where arginine hydrochloride corrects the Cl deficiency and returns the alkalosis toward normal). We therefore do not expect any acidosis, but will monitor serial real-time venous pH, PCO2, chloride and bicarbonate at the bedside using iSTAT EC8+ cartridges.

Response: Arginine infusion will be ceased if venous bicarbonate falls below 15 mmol/L.

*c)* *Effect on kidney function:* We can find no case reports or primary clinical studies that report renal toxicity with L-arginine. In fact, two recent studies show that renal blood flow and glomerular filtration rate (the most accurate measure of renal function) **improve** after the infusion of L-arginine. Schlaich et al,59 studied patients with normal renal function and used an intravenous infusion of L-arginine at doses of 100mg/kg (7 Grams for a 70 kg adult) and 500mg/kg (35 grams for a 70 kg adult) over 30 minutes. They showed a statistically significant ***improvement*** in both renal blood flow and glomerular filtration rate at each dose. In the second study60, n intravenous dosage of 17mg/kg gave the same improvement in normal subjects. Reassuringly, in patients with renal impairment in this study, arginine infusion was safe and **did not** cause any worsening of renal blood flow or glomerular filtration rate. We therefore do not expect any change in renal function in studies 2 and 3, but we will monitored renal function by serial iSTAT bedside biochemistry (see Table 2).

*d) Consequences of tissue NO production from tissue NOS.* We believe that tissue NO production will have tissue-protective effects and will also reduce generation of superoxide from arginine-deficient NOS. Nevertheless we will be able to detect unexpected deleterious effects of increased tissue NO. As well as the organ-specific biochemical markers above (including creatinine, creatine kinase and liver enzymes/bilirubin), our existing lung function laboratory at RSMM and the exhaled NO apparatus will give us the unique opportunity to relate exhaled NO to measures of pulmonary gas transfer and alveolar dead space, sensitive markers of lung injury.

In the current sickle cell disease trial in the US children with acute vaso-occlusive disease, 36 patients (age 4-18 years) have been randomized to IV arginine 0.1 g/kg vs placebo. This has been very well tolerated, with no significant effect on blood pressure, liver function tests, electrolytes, glucose, renal function or vital signs ([name], personal communication 2004). There have been no serious adverse events, and no acidosis

**Serious adverse events:** The following adverse events will be deemed serious, and will be notified immediately to the Chief Investigators and to the Chair of the Data Monitoring Committee for immediate review:

1. Death
2. Serum K+ rising > 6.0 meq/L with ECG changes
3. Anaphylaxis
4. SBP falling below 80 mmHg unresponsive to saline infusion
5. Clinical requirement for admission to High Care Unit, dialysis or ventilation

The doctor responsible for immediate management of adverse effects will be the internal medicine residents from Manado, currently [name]. These are very experienced senior internal medicine residents.

**Limitations of Study 1 and 2:** Only patients with Hb≥6g/dl are included in this study. We do not believe that the PK-PD relationship will be significantly different in severe malarial anemia than in other forms of severe malaria, but cannot exclude this. Once the PK-PD relationship in severe malaria is known, in future studies we may be able to confirm its similarity in severe malaria anemia with fewer blood draws.

**Study 3:**

***Randomised concentration controlled trial, safety, and pharmacokinetic study in uncomplicated malaria:***The pharmacokinetic-pharmacodynamic model [from studies 1 and 2)] will be used to determine an appropriate loading and maintenance dose of arginine in uncomplicated malaria, to achieve average plasma arginine concentrations of ~600 uM (a plasma level ~4 times the Km of CAT2 transporters for cellular uptake of extracellular arginine). *Prior to the commencement of study 3, the Data Monitoring Committee will review the dosing and sampling schedule we will calculate from the pharmacokinetic-pharmacodynamic model generated in studies 1-2.* In addition, the target concentration (600 mcM) may need to be readjusted based on the results from studies 1 and 2.

*Design:* Randomised Concentration Controlled Trial.

*Treatment allocation:* Patients with uncomplicated malaria will be randomized to receive one of two treatments:

i) Standard RSMM antimalarial drug regimen for falciparum malaria (currently quinine) plus normal saline placebo (loading dose of 100 ml over 30 mins plus maintenance infusion using same volume in [ii] below).

ii) Standard RSMM antimalarial drug regimen for falciparum malaria (currently quinine) plus IV arginine: loading dose as 30 min infusion (see CRF) followed by maintenance infusion over 12 hours. The doses of arginine will be determined from the pharmacokinetic-pharmacodynamic model to maintain a plasma level of 600uM.

An independent statistician will use computer-generated randomization to generate blocks of patient numbers for each treatment.

*Sample size:* Extrapolating from similar concentration controlled trials, we estimate approximately 20 subjects in each of the two groups. Sample size calculation will require the results of the natural history of arginine/NO/NOx levels during malaria (study 1), and the maximal improvement and time course of improvement following administration (study 2). Therefore the final sample size will be calculated based on the results of studies 1 and 2. The sample size will be reviewed by the Data Safety and Monitoring Committee, and each of the relevant ethics Committees will be notified prior to commencement of Study 3 with confirmation of the number of patients.

*Patient numbering and randomization*:

Once the patient has a confirmed diagnosis of falciparum malaria, has fulfilled all the inclusion criteria, has none of the exclusion criteria and has given written informed consent to participate, he/she will be allocated the next code of the study.

Randomization will be carried out in groups of 10, and each code given a sealed opaque envelope which will contain that patients’ treatment group and which will only be opened when a patient has been allocated a code number.

*Design:*

Cannula insertion and baseline sampling will be performed as in study 2. Serial vital signs, clinical assessments, and laboratory parameters of safety will be measured as in Study 2 above. As appropriate, we will use the model generated from studies 1 and 2, and modeling of any electrolyte disturbances to optimize the sampling schedule ***which will result in a reduced total number of pharmacokinetic and pharmacodynamic blood samples required compared with study 2***. The maximum total volume of blood drawn will again be ≤25ml, but because of reduced numbers of samples will likely be less. In addition we will measure preliminary biomarkers of efficacy: fever and parasite clearance times, serial lactate levels, plasma levels of endothelial adhesion molecules, biomarkers of inflammation and effects on physiological parameters (including vascular function, gas transfer and physiological deadspace), with frequency again guided by results from studies 1 and 2. The effect on NO production will be examined by serial measures of plasma NOx/creat, and exhaled NO, and effect on oxidant stress, including serial plasma glutathione (GSH):oxidised glutathione (GSSG) ratios (by HPLC)61.

Observations will continue for 24 hours after the completion of the arginine infusion, with the final assessment at this time being identical to the final assessment in study 2.

*Outcomes:*

In the arginine-treated group there will be global improvements in both biochemical (including plasma NOx/creatinine, exhaled NO) and physiological markers (including brachial artery dilatation, hyperemic blood flow on Doppler and physiological deadspace).

*Interpretation:* This data will generate more safety data in uncomplicated malaria. The data will be used to refine the linked pharmacokinetic-pharmacodynamic (pharmacokinetic-pharmacodynamic) model, with arginine levels being related to measures of NO production and oxidant stress as above. Determining if exogenous arginine results in an increment in NO production in malaria (± reduction in oxidant stress) and physiological parameters to be tested would be a major advance. It is hypothesised that arginine will result in improvements in clinically important outcomes in *severe malaria*. Because uncomplicated malaria is by definition a milder disease than severe malaria we do not necessarily expect to be able to detect improvements in clinically relevant outcomes in this study of uncomplicated malaria patients. We may be able to generate data on preliminary efficacy using biomarkers of outcome (eg lactate levels) in uncomplicated malaria, however lactate levels are usually only modestly elevated (or normal) in mild disease. An effect on lactate level will be sought but will not be required as part of the decision-making for proceeding to study 4 in severe malaria (where such an effect ***is*** expected).

*Feasibility:* RSMM has a clinical research unit attached to its intensive care unit. As part of our ongoing severe malaria studies, RSMM-MSHR-NIHRD research staff are experienced in assessing patients for fulfilment of modified WHO criteria for severe malaria and ensuring consent is informed by a thorough explanation of the study. The laboratory at RSMM has a dedicated research microscopist/technician, -70ºC freezer, refrigerated centrifuges and biosafety cabinet, and the bedside iSTAT apparatus can rapidly assay biochemical measures of safety. Supervision and quality assurance of exhaled NO, vascular and lung physiology will be undertaken by experienced collaborators. Our team members in Timika are fully familiar with lung function tests as part of our current lung-malaria studies. Pharmacokinetic-pharmacodynamic modeling, and protocol design for study 3 will be done under the supervision of an experienced pharmacometrician ([name]), statistician ([name]) and [name] (NIHRD).

*Proposed timeline (subject to ethics approval process):*

October 2004: planning visit, finalisation of logistics, setting up exhaled NO apparatus, deadspace equipment and troubleshooting equipment.

Dec 2004- Nov 2005: study 1 *(subject to ethics approval process):*

Dec 2004 -April 2005: Study 2

Feb 2005- Oct 2005: measurements of arginine, and NOx:creat

April-August 2005: PD-PD modelling. Design of study 3: review by Data Safety Monitoring Committee

Dec 2005- April 2006: Study 3.

Nov 2005- mid 2006: measurements of arginine, and NOx:creat; further PK-PD modelling. Design of Study 4 (severe malaria) to be submitted to ethics for review.

*Ethics*

Studies 1-3 above will be reviewed by the Ethics Committee of National Institute of Health Research, Ministry of Health, Jakarta, Indonesia and the Ethics Committee of Menzies School of Health, Darwin, Australia. The data generated in studies 1-3 will be used to decide whether proceeding to a study in *severe malaria* is warranted, and if so, to design an appropriate protocol for undertaking the safety and pharmacokinetic-pharmacodynamic study in *severe* malaria. The future severe malaria protocol will be submitted to each of the Ethics Committees as a separate future submission based on the results from studies 1-3.

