**Please see Appendix 3 for the types of physiological tests that will be done and where they will be done.**

**Study 2**

***Pilot pharmacokinetic, pharmacodynamic and safety study of exogenous arginine in uncomplicated falciparum malaria:***

*Overview:* In this pilot study in uncomplicated malaria we will generate initial safety, pharmacokinetic and pharmacodynamic data for exogenous arginine administration. We will use a dose-escalation design; all doses (3-12g) will be in the low-mid range of dosages previously used safely in humans (6-30g). *Dosing:* All doses of arginine hydrochloride will be infused intravenously over 30 mins (which is the standard infusion time). Initial dosing will be 3g (n=10), increasing to 6g (n=10), increasing to 12g (n=10) if lack of significant toxicity is demonstrated at each dosing level. Each arginine dose will be added to 100ml normal saline (the standard diluent safely used in other studies) such that total concentration is ≤10% (see CRF)

In addition to arginine, all subjects will be treated with standard antimalarial drugs (currently quinine) as per standard RSMM/Depkes practice/protocols.

*Clinical measures.* Vital signs (pulse rate, BP, temperature, respiration rate), and a standardised clinical assessment (symptom/sign list) will be serially monitored over 48 hours (see table 2). ECG will be monitored from -60 to 240 mins.

*Blood sampling*:

Two venous cannulae will be placed:

A cannula in the right forearm will be used for administration of IV arginine, and for any IV fluids required after arginine administration.

A cannula in the left forearm or antecubital fossa for sampling of venous blood, placed one hour prior to arginine adminstration.

At the time of cannula insertion we will take 7 ml heparinised baseline blood. This will be the -60 minute sample: 60ul will be used for baseline iSTAT EC8+ measurement of electrolytes, glucose, urea, and bicarbonate. The remainder will be processed as per NO Study II SOP for heparinised blood.

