*Interpretation:* Pharmacokinetic models will be fitted to concentration-time and concentration-effect data from studies (a) and (c) using NONMEM (v. 5)51, to provide population parameter estimates, mean parameter values and their between-subject variability where possible. This analysis will include assessment of possible covariate relationships, where parameter values such as clearance may be correlated with patient demographics such as age. A model will be developed that describes the time course of effects of arginine in terms of NO production (plasma NOx/creatinine ratio [systemic NO production] and exhaled NO [pulmonary NO production]), oxidant stress, endothelial function, microvascular flow and gas transfer/physiological deadspace. It is also intended to address biomarkers of effectiveness. **[name] from NIHRD will be invited to the Dept Pharmacy in Brisbane to join the NONMEM modeling for the PK-PD relationships outlined above.**

Safety data from study 2 will be reviewed by an experienced independent data monitoring committee (see appendix) before proceeding to study 3. The pharmacokinetic-pharmacodynamic model developed in study 2 will enable us to predict the dosing and best sampling schedule (both pharmacokinetic and pharmacodynamic) for use in study 3. If the pharmacokinetic-pharmacodynamic model suggests that a higher dose than 12g may be required, a dose of up to 18 g may tested in stage 2 of the study prior to commencing stage 3.

*Potential adverse effects (in study 2 and study 3) and study response:* A number of adverse effects have been previously noted with large *supraphysiological* dosing in subjects with normal plasma arginine levels. These have been infrequent and usually at the standard high dose (≥30g) required to stimulate growth hormone release, **a *dose that will not be used in our studies.*** Arginine is a natural product that has been widely used in subjects with cardiovascular disease, sickle cell disease, and sepsis, with an excellent safety profile. This study primarily examines pharmacokinetic-pharmacodynamic modeling, but will also confirm safety in uncomplicated malaria.

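### Study 3 is the first to give a 12-hour arginine infusion, but no cumulative by-arm safety review is scheduled during it, and several events that stop an infusion need not reach the committee

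*Combined protocol and SAP*

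**What the plan says.** **Regimens.** Study 2 (Dosing) states "All doses of arginine hydrochloride will be infused intravenously over 30 mins", at 3, 6 and 12 g with 10 patients each. Its Interpretation paragraph allows up to 18 g if the model calls for it. Escalation is stepwise: "increasing to 12g (n=10) if lack of significant toxicity is demonstrated at each dosing level". Study 3 (Treatment allocation) gives a 30-minute load "followed by maintenance infusion over 12 hours", with doses taken from the model to hold about 600 uM.

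**Committee review before Study 3.** Study 2 (Interpretation) says "Safety data from study 2 will be reviewed by an experienced independent data monitoring committee". Study 3 adds "Prior to the commencement of study 3, the Data Monitoring Committee will review the dosing and sampling schedule", and the committee also reviews the final sample size.

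**Committee review during Study 3.** The adverse-effects section covers Studies 2 and 3. Its serious adverse events paragraph lists five event types, which "will be notified immediately to the Chief Investigators and to the Chair of the Data Monitoring Committee for immediate review". The same section sets limits at which an individual patient's infusion is stopped.

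**Allocation.** Study 3 says "Randomization will be carried out in groups of 10", with about 20 patients per arm as a provisional size.

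**The concern.** The regimen that matters for later work in severe malaria is first given to malaria patients in Study 3. Study 2 has a toxicity check between dose levels, but the text available has no equivalent step once the longer infusion begins. If that infusion were poorly tolerated in ways short of a listed serious event, all of the roughly 20 arginine patients could be treated before anyone independent saw the pattern. Studies 1-3 are also the stated basis for deciding whether to proceed to severe malaria, and the text does not say that the committee sees the completed Study 3 safety data before that decision.

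**Working it through.** The provisional 20 per arm is given without alpha, power, effect size or standard deviation, so it cannot be reproduced. It is used here as stated.

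**1. Duration.** Study 2: 30 minutes. Study 3: 30 + 720 = 750 minutes. No Study 2 patient receives a maintenance phase.

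**2. Amount implied by the Study 3 target.** Inputs: 600 uM (Study 3); clearance 544-1018 ml/min (Background, clinical pharmacology); 4.75 mEq of H+ per gram of arginine hydrochloride (Effect on pH); 720 minutes. Assumptions: constant clearance, level held throughout, one mEq of H+ per mmol of arginine.

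Amount = concentration x clearance x time:
- Low: 0.600 mmol/L x 0.544 L/min x 720 min = 235 mmol; 235 / 4.75 = 49.5 g, or 4.1 g/h.
- High: 0.600 x 1.018 x 720 = 440 mmol; 440 / 4.75 = 92.6 g, or 7.7 g/h.
- Crediting endogenous arginine of 114 uM at the low end (486 uM to supply) and 54 uM at the high end (546 uM) gives 40.1 g and 84.3 g.

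All figures exclude the load. Against 12 g, they are about 3.3 (40.1/12) to 7.7 (92.6/12) times the planned Study 2 maximum, at a slower rate.

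**3. Which infusion-stopping events reach the committee?**

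| Stops the infusion | On the serious event list? |
|---|---|
| Systolic fall >25 mmHg, or below 80 mmHg | Only if below 80 and unresponsive to saline |
| K+ ≥6.0 meq/L, or significant ECG changes | Only if K+ >6.0 with ECG changes |
| Glucose <4 mmol/L | No |
| Bicarbonate <15 mmol/L | No |
| Rash; extravasation | No |
| Anaphylaxis | Yes |

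Any of these would be notified if it led to death, High Care Unit admission, dialysis or ventilation. Otherwise the events marked No, and the milder forms in the first two rows, have no stated route to the committee.

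**4. What the data could show.** With zero events in n patients, the one-sided 95% upper limit is 1 - 0.05^(1/n): 25.9% for 10 (one Study 2 dose level), 9.5% for 30 (all of Study 2) and 13.9% for 20 (the Study 3 arginine arm). The Study 2 limits describe 30-minute infusions only.

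A review after the first group of 10 covers about 5 arginine patients if the group is balanced. The chance of at least one infusion stop among 5 is 1 - (1 - p)^5. The chance of at least two subtracts a further 5p(1 - p)^4. The rates p are assumed; the documents give none.

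| Assumed rate | At least 1 of 5 | At least 2 of 5 |
|---|---|---|
| 10% | 41% | 8% |
| 20% | 67% | 26% |
| 30% | 83% | 47% |

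Such a review would catch a clearly intolerable regimen while about 15 of 20 arginine patients remain to be treated. It would not exclude a moderate rate.

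**The case against.** The strongest reply is that oversight is already layered. Each patient has infusion-stop limits. The committee sees Study 2 safety data and the Study 3 dose, sampling schedule and size before the start, and its Chair is told at once of the gravest events. The documents expect adverse effects to be very unlikely. They also report 36 sickle-cell patients randomised to IV arginine or placebo with no serious events. Study 2 cites a committee appendix that is not in the text available, which could hold review times and pause rules. This stands in part: absence from the plan cannot be proved, and the point is conditional on that appendix.

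A reader might infer more than the documents support:

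- **That the committee reviews only the design.** It also reviews Study 2 safety data and receives the five event types during Study 3.
- **That nothing could pause Study 3.** A Chair's review might lead to a pause. The text simply attaches no consequence or allocation hold to it.
- **That severe malaria would be entered without independent scrutiny.** The Ethics paragraph sends any such protocol to the ethics committees as a separate submission, and the glucose paragraph promises them those findings first.
- **That Study 3 will break a dose limit.** The 30 g sentence concerns the standard high dose used to stimulate growth hormone. The range above is a 12-hour total, from clearances measured after large doses in adults with normal arginine. The protocol reports non-linear kinetics and lets the target be readjusted.
- **That a fixed pause count should be written in now.** A pause at the second arginine-arm stop shows the difficulty. The chance of at least 2 among 20 is 26% at a true rate of 5%, 61% at 10% and 93% at 20%. The last applies even if saline patients meet the same limits equally often, because one arm alone is counted.

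**Conclusion.** The point holds as a gap in planned oversight. Study 3 introduces an infusion lasting 750 minutes after a pilot of 30-minute infusions, and the implied maintenance total lies well outside what Study 2 covers. During Study 3, the text provides case-by-case notice of five event types but no scheduled cumulative review by arm. Several infusion-stopping events fall outside that notice.

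The first two statements follow directly from the documents. The 49-93 g range depends on the clearance and steady-level assumptions in the working. The detection probabilities rest on assumed event rates and on a balanced first group. Confidence is moderate because the committee appendix was not available. The improvement is worth making because it is cheap and bears on patient safety. It does not show that the regimen is unsafe.

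**What to change.** Add to Study 3:

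1. The existing committee reviews cumulative Study 3 safety data by arm after the first randomisation group of 10, before the next group's envelopes are opened. It does so again at the end of Study 3, before the decision on severe malaria.
2. These reports include every infusion stopped under the limits already in the adverse-effects section, whether or not the event is on the serious list. The clinical limits stay unchanged.
3. Before Study 3 starts, the committee itself sets any threshold for pausing allocation, taking both arms into account, and states whether allocation holds while a serious event is under review.

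The interim report is for safety only, with no efficacy comparison, so it needs no adjustment of the significance level.

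Separately, reconcile the Study 2 statement on the 30 g dose with the Study 3 target of 600 uM over 12 hours, saying whether that statement refers to a single infusion or to the total given.

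If the committee appendix already covers items 1-3, a cross-reference in Study 3 suffices. Otherwise the cost is one or two short reviews by the existing committee and a brief pause in a trial of about 40 patients, with no new tests.

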Response: Moderate hypophosphatemia (1-2.5 mg/dL) is almost always asymptomatic and requires no therapy. Moreover, transient hypophosphatemia following arginine infusion *will not reflect any depletion of total body phosphate* that is required for very low levels of plasma phosphate to cause clinical manifestations. Low phosphate will therefore not be treated unless deemed essential by the treating clinician.

*c)* *Thrombophlebitis* is very unusual, but has been described57. This is minimized by using ≤10% solutions. One episode of *an extravasation reaction* has been described in a child. This will be minimized by administering arginine as a 10% solution, and careful insertion and observation of IV canula/symptoms/signs during infusion.

Response: If extravasation occurs, the infusion will be stopped, the affected extremity elevated. The catheter/needle will not be removed immediately, but rather left in place to aspirate fluid from the extravasated. The line will then be removed and an ice pack applied.

*d)* *Anaphylaxis*: We are aware of only one report of a case of *anaphylaxis58*. This would seem a very rare event with an exogenous/endogenous amino acid and is considered extremely unlikely in current studies

Response: The arginine infusion will be ceased. Adrenaline and rescucitation facilities will be readily available in the high care unit at RSMM, to which the clinical research ward is attached. Standard treatment for anaphylaxis will be undertaken in the very unlikely event it would be required.

*e)* *Rash:* maculopapular rash: rare; causality not proven. Response: infusion will be stopped

*f) Minor adverse effects:* Arginine can uncommonly cause nausea, vomiting, flushing, headache, and numbness. These will be documented in the CRF. These are also common in malaria, and will not result in cessation of the infusion, unless patient requests to withdraw from the study. In previous studies with oral arginine in SCD, gastrointestinal symptoms (including abdominal cramping and diarrhea) were occasionally seen ([name], personal communication 2004), one of the reasons why they are now using IV arginine for the ongoing trial in SCD. Gastrointestinal side-effects (eg nausea, vomiting) have not been seen with IV infusion in SCD. Minor flushing has been seen.

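### The Study 3 saline load is fixed at 100 ml while the arginine load is still to be set, so the loading infusions are not ensured to match and cannot match above 10 g within the 10% limit

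*Combined protocol and SAP*

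**What the plan says.** Study 3, Treatment allocation, describes the control infusion as "normal saline placebo (loading dose of 100 ml over 30 mins plus maintenance infusion using same volume in [ii] below". The arginine arm receives a "loading dose as 30 min infusion (see CRF) followed by maintenance infusion over 12 hours". No loading volume or diluent is given for that arm, and the dose is open: "The doses of arginine will be determined from the pharmacokinetic-pharmacodynamic model to maintain a plasma level of 600uM".

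The only preparation volume for arginine is under Study 2, Dosing: "Each arginine dose will be added to 100ml normal saline", "such that total concentration is ≤10% (see CRF"). Study 2 plans 3, 6 and 12 g. Study 2, Interpretation, adds that "a dose of up to 18 g may tested in stage 2" if the model points that way.

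The 10% ceiling is not confined to Study 2. The discussion of adverse effects is introduced as covering Studies 2 and 3. Its item (c), on thrombophlebitis and extravasation, limits solutions to at most 10% and then says of extravasation: "This will be minimized by administering arginine as a 10% solution".

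**The concern.** The authors clearly had volume matching in mind, because they wrote it for the maintenance infusion. They did not write it for the load, where one arm has a fixed volume and the other depends on a dose not yet chosen. A fixed figure can equal a variable one only by luck or by a further rule, and the protocol text gives no such rule.

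At stake is the value of the saline as a placebo. If the loading bag is larger or the pump runs faster in one arm, patients and staff can tell which arm it is. Study 3 expects about 20 patients per group. Its outcomes include brachial artery dilatation and Doppler hyperaemic flow, which depend on the operator and are open to observer bias. A secondary worry is that the arms would receive different amounts of fluid shortly before haemodynamic readings.

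**Working it through.** The 100 ml is a specification, not a derived figure, so there is nothing to reproduce. The check asks when an arginine load can share it.

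**Inputs**
- Placebo load: 100 ml over 30 min (Study 3, Treatment allocation), which is 200 ml/h.
- Arginine load: 30 min, volume not stated (same place).
- Ceiling: at most 10%, taken as 10 g per 100 ml (Study 2, Dosing; adverse effects, item c).
- Doses named: 3, 6 and 12 g, with 18 g possible in stage 2.
- Clearance 544–1018 ml/min and half-life 40–120 min (Background, clinical pharmacology); 4.75 mEq per g of arginine hydrochloride (effect on pH), so 1000/4.75 = 210.5 g/mol.

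**Step 1. If 100 ml is the final arginine volume.** Concentration (%) = dose in g / 100 ml × 100.
- 3 g gives 3%, 6 g gives 6% and 10 g gives 10%. The ceiling is met, and volume and rate equal the placebo's.
- 12 g gives 12% (10.7% even if counted as 12/112), and 18 g gives 18% (15.3% as 18/118). The ceiling is broken.

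**Step 2. If the ceiling is kept.** Minimum volume = dose / 0.10 g per ml; rate = volume × 2 per hour.

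| Load | Minimum volume | Rate | Excess over placebo |
|---|---|---|---|
| 10 g | 100 ml | 200 ml/h | none |
| 12 g | 120 ml | 240 ml/h | 20% |
| 18 g | 180 ml | 360 ml/h | 80% |

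Above 10 g, a 100 ml bag and the ceiling cannot both hold.

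**Step 3. If drug is literally added to 100 ml of saline.** Total volume = 100 + dose / stock strength, which exceeds 100 ml at every dose. The documents give no stock strength, so the excess cannot be stated. It may be trivial: for dry powder with an assumed displacement of 0.7 ml/g, 3 g gives 102.1 ml and 6 g gives 104.2 ml.

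**Step 4. If item (c) means exactly 10%.** Volume = dose / 0.10: 30 ml for 3 g, 60 ml for 6 g and 120 ml for 12 g. Only a 10 g load would then equal 100 ml. The same paragraph also gives 10% as an upper limit, so this reading is uncertain.

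**Step 5. Could the Study 3 load exceed 10 g?** This is a range check, not a proposed dose. It assumes one compartment, a bolus, and a rise from 54 to 600 µM. V = CL × half-life / ln 2; load = 546 × 10⁻⁶ mol/L × V × 210.5 g/mol.

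| CL (ml/min) | Half-life (min) | V (L) | Load (g) |
|---|---|---|---|
| 544 | 40 | 31.4 | 3.6 |
| 1018 | 40 | 58.7 | 6.8 |
| 544 | 120 | 94.2 | 10.8 |
| 1018 | 120 | 176.2 | 20.3 |

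The range lies on both sides of 10 g.

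**Step 6. Size of the fluid difference.** Against an assumed plasma volume of 3 L, an extra 20 ml is 20/3000 = 0.7% and an extra 80 ml is 80/3000 = 2.7%.

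**The case against.** A reader might infer that the two arms will receive different loading volumes. The documents do not say so. The instruction to add the drug to 100 ml belongs to Study 2. The Study 3 load refers to a case report form that is not available here, and details held there cannot be counted as missing. The placebo's 100 ml equals the Study 2 diluent volume, which suggests that matching was intended, and loads up to 10 g in a 100 ml final volume do match. The 18 g figure is a contingent Study 2 dose, not a Study 3 load. The Data Monitoring Committee is to review dosing before Study 3 begins.

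A reader might also take the 10% in item (c) as the strength of a stock that is then added to 100 ml, and so compute much larger volumes. That item describes the solution as administered, and no stock strength is given, so such volumes have no support.

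On masking, the Study 3 text states no blinding procedure, and the sealed envelope discloses the treatment group once a code number is allocated. Harm to staff masking is therefore inferred; only the word placebo points to masking at all. On confounding, the likely extra volumes are small, the 12-hour maintenance infusion is already matched, and the NOx/creatinine and GSH:GSSG ratios are largely insensitive to dilution. Table 2 tests endothelial function 15 min after the infusion ends, but Study 3 leaves measurement frequency to the results of Studies 1 and 2. The range in step 5 pairs extremes of clearance and half-life in a simple model, although the Background reports apparent non-linear kinetics.

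All of this stands, and it limits the point. It does not remove it: a printed, fixed placebo volume cannot be guaranteed to match a load still to be chosen, and the 10% ceiling reaches Study 3 through the adverse-effects section without borrowing the Study 2 preparation text.

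**Conclusion.** The point holds in a conditional form. The protocol does not ensure that the loading infusions match. A mismatch is forced only if the load exceeds 10 g and the ceiling is kept, with at least 20% more volume at 12 g and 80% more at 18 g. At or below 10 g it depends on how the load is prepared. That a load above 10 g is possible rests on the one-compartment assumption and the protocol's reported ranges; it is not a prediction.

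The main consequence is a recognisable placebo, which would undermine any masking of patients or of those measuring vascular function. Fluid confounding is probably minor. Separately, the planned 12 g dose in Study 2 already sits awkwardly with a 100 ml preparation and a 10% ceiling, so those statements need reconciling whatever load Study 3 uses.

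**What to change.** In Study 3, Treatment allocation, tie the placebo loading volume to the arginine loading volume in arm (ii), as the text already does for maintenance. Reconcile Study 2 Dosing, item (c) of the documented adverse effects, and Study 3 Treatment allocation, so that the stated preparation volume and the 10% limit are compatible at every dose level used. Carry the result into the case report form for both arms. How they are reconciled is for the sponsor and its clinical and pharmacy advisers; no dose, volume or concentration is proposed here.

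The cost is a short protocol clarification and matching case report form entries, with no extra patients or procedures. The placebo volume would then follow whatever active load is chosen. The change is needed before Study 3 starts, because mismatched infusions cannot be corrected in the analysis.
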